### Study sample

Participants will be included in the analysis if they have downloaded the app onto an iOS smartphone or tablet, are 18 years of age or over, live in the United Kingdom and have an AUDIT score of 8 or above (indicative of excessive alcohol consumption), have confirmed that they are making an attempt to reduce their drinking (responded “Interested in drinking less alcohol”, not “Just browsing” to “Why are you using this app?”), and provided an email address.

This study will recruit 672 participants and have more than 80 % power (with alpha at 5 %, 1:1 allocation and a two-tailed test) to detect a mean change in alcohol consumption of 5 units between the high and low condition for each intervention module [109]. This assumes a mean of 27 weekly units at follow-up in the control group, a mean of 22 units in the intervention group and a SD of 23 units for both (d = 0.22), and rounds up the sample size to the nearest multiple of 32 to ensure all cells are balanced. The estimated effect size is large (comparable with that of a face-to-face brief intervention [5]) and may be considered somewhat unrealistic for a module within a digital intervention. However, in the event of a ‘non-significant’ result, we plan to calculate a Bayes factor to establish the relative likelihood of the null versus the experimental hypothesis given the data obtained [110]. This will permit a relative judgment for the purposes of screening about whether the inclusion of the module in a future app would be more likely than not to have an effect on alcohol consumption.

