### Outcome measures

The primary outcome measure is change in past week consumption of alcohol; calculated from the AUDIT-C score at baseline and 1-month follow-up [109]. Secondary outcome measures will be i) change between baseline and follow-up on the full AUDIT score ii) app usage data (user sessions per day, screen views per day, screens per session, session duration and session instances, user retention), and iii) usability ratings for the app (a) how helpful did you find Drink Less? b) how easy did you find Drink Less to use? c) how satisfied are you with Drink Less? d) how likely are you to recommend Drink Less to a friend?). An intention-to-treat approach will be used such that those who are lost to follow-up will be retained in the primary analysis and assumed to be drinking at baseline levels. The full 10-item AUDIT assesses alcohol consumption (AUDIT-C), harmful drinking and alcohol dependence [116]. The AUDIT has been used in other trials for assessing alcohol consumption and related harms [117].

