### Analysis

A factorial between-subjects ANOVA will be conducted to assess main and interactive effects of the five intervention modules on the primary and secondary outcomes. In a sensitivity analysis, ANCOVAs will also be conducted to adjust for any chance imbalances in drinking and socio-demographic characteristics (gender, age, ethnicity, level of education, employment status, AUDIT score, AUDIT-C score).

On the basis of the intention-to-treat principle, individuals who are not followed up (non-responders) will be retained in the analyses and assumed they drinking at same levels as baseline. Sensitivity analyses will be conducted i) among only those who completed the follow-up questionnaire (responders) and ii) by imputing missing data from baseline characteristics. The intention-to-treat principle is often used in digital public health interventions [118–120] and is a conservative approach to ensure effect sizes are not over-estimated as participants who respond well to the intervention are more likely to be retained.

In the event of a non-significant main effect of an intervention module, Bayes factors will be calculated with the alternative hypotheses conservatively represented in each case by a half-normal distribution (online calculator: http://www.lifesci.sussex.ac.uk/home/Zoltan_Dienes/inference/Bayes.htm). In an alternative hypothesis represented by a half-normal distribution, the standard deviation of a distribution can be specified as an expected effect size, which means plausible values have been effectively represented between zero and twice the effect size, with smaller values more likely. The expected effect size for the primary calculation of Bayes factors will be the same as for the power calculation (d = 0.22). In a sensitivity analysis, we will also calculate Bayes factors for a smaller effect (reflecting a reduction of 3 units per week, d = 0.13).

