Our power calculation relied on a large estimated effect size (comparable with that of a face-to-face brief intervention) and may be considered somewhat unrealistic for a module within a digital intervention. The reason is that selecting smaller effect sizes would require larger numbers of participants and more time to recruit them. The Multiphase Optimization Strategy, which guides our research, emphasises agile screening experiments before running a definitive head-to-head trial of an optimised intervention against a control [106, 124]. We deal with the limitation of a somewhat unrealistic effect size for our power calculation by planning to supplement our inferential statistics by calculating Bayes factors. Bayes factors will provide useful information on the relative likelihood of smaller (more realistic) effects compared with the null given the data we obtain.

One strength of this intervention is that it is delivered by smartphone, so there will be no issues of availability or accessibility for the participants. The app can be used fully without an internet connection. The data is stored on the phone until an internet connection is available, when the data is then sent to the server. A limitation of this type of study is high attrition. We will send regular reminders for the one-month follow-up questionnaire and remind them of the incentives offered to reduce the risk of attrition. A practical issue may be recruiting enough participants to meet the numbers sufficient to meet the power for our analysis. We have planned for this issue by using best practices for app store optimisation and by promoting the app through trusted organisations such as Public Health England and University College London.

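### The Bayes factors drift towards the null as loss to follow-up rises, because the alternative is not scaled to the share of participants who respond

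*Protocol article*

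**What the plan says.** - **Missing outcomes.** Under Outcome measures, "those who are lost to follow-up will be retained in the primary analysis and assumed to be drinking at baseline levels". The Analysis section repeats the rule and calls it conservative, because it guards against over-estimating effects.
- **Bayes factors.** The Analysis section says: "In the event of a non-significant main effect of an intervention module, Bayes factors will be calculated with the alternative hypotheses conservatively represented" by a half-normal distribution. The standard deviation of that distribution is the power-calculation effect, d = 0.22. A sensitivity version uses 3 units a week, d = 0.13.
- **Origin of the 5 units.** Study sample states: "This study will recruit 672 participants and have more than 80 % power". The difference sought for every module is 5 units, from 27 at the low level to 22 at the high level, taking the SD as 23 (hence d = 0.22), a two-sided 5% test and equal allocation. The only adjustment to the number is rounding up to a multiple of 32.
- **Attrition.** The Discussion says: "A limitation of this type of study is high attrition". No rate is given.
- **Other analyses.** Responder-only and imputed sensitivity analyses are planned, but the Bayes factors are not linked to either.
- **Purpose.** Study sample and Discussion present the Bayes factor as the answer to an admittedly optimistic effect size, and as the basis for judging whether a module belongs in a future app.

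**The concern.** The estimate and the alternative it is compared with appear to be on different footings. A main effect computed with zeros for non-responders shrinks as response falls. The alternative does not, because it comes from a calculation with no visible allowance for loss to follow-up.

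The no-change rule is conservative when the question is whether to claim an effect. It is not conservative for a statistic that may be used to support no effect, since there it pushes towards the verdict being sought. At stake is the screening decision: a module that works could be set aside on evidence for the null that partly reflects non-response.

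**Working it through.** **The plan's own figure.** With a difference of 5, SD 23, two-sided 5% and 80% power, n per level = 2 × (1.96 + 0.84)² × 23² / 5² ≈ 332.2, so 333 per level and 666 in all. Rounded up to a multiple of 32 this is 672, with power 80.4%. The figure reproduces with no inflation for dropout.

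**Inputs.** From the protocol: 336 per level, SD 23, effects of 5 and 3 units. Assumed here: response proportion p equal at both levels; SD 23 applies to responders' change; responders at the low level fall by 5 units; non-responders would have benefited as responders did.

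**Formulas.**
- Expected carried-forward difference: x = p × (true effect).
- Variance of change at a level with mean responder fall m: p(23² + m²) − (pm)².
- SE = √[(variance at low + variance at high) / 336].
- Bayes factor with half-normal SD τ: BF = 2 · N(x; 0, SE² + τ²) · Φ(xτ / (SE√(SE² + τ²))) / N(x; 0, SE²).

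**Worked case: 50% response, true effect 5.** x = 2.5. Low level (m = 5): 0.5 × 554 − 6.25 = 270.75. High level (m = 10): 0.5 × 629 − 25 = 289.5. SE = √(560.25 / 336) = 1.29. With τ = 5, BF equals 1 at an observed difference of 1.69, so P(BF<1) = Φ((1.69 − 2.5) / 1.29) = 26%. With τ = 5 × 0.5 = 2.5, BF equals 1 at 1.17, so P(BF<1) = Φ((1.17 − 2.5) / 1.29) = 15%.

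**True effect 5, by assumed attrition.** Rescaled means τ = 5p. The d-scale column uses τ = (5/23) × the SD of the carried-forward change.

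| Attrition | x | SE | BF at x: τ = 5 | BF at x: rescaled | P(BF<1): τ = 5 | P(BF<1): rescaled | P(BF<1): planned 3 units | P(BF<1): d = 0.22 |
|---|---|---|---|---|---|---|---|---|
| 30% | 3.5 | 1.51 | 6.7 | 7.5 | 14% | 9.5% | 8% | 12% |
| 50% | 2.5 | 1.29 | 2.8 | 3.9 | 26% | 15% | 18% | 21% |
| 70% | 1.5 | 1.01 | 1.06 | 2.1 | 49% | 23% | 37% | 36% |

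**Further results at 70% attrition.**
- True effect 5: P(BF<1/3) is 18% with τ = 5, 8% with the planned 3 units, 7% on the d scale and 0.8% rescaled.
- True effect 3: P(BF<1/3) is 38% with τ = 5, 20% with the planned 3 units and 4% rescaled.

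**Source of the gap.** A responders-only estimate against the 5-unit alternative gives expected BFs of 8.1, 4.2 and 2.3 at 30%, 50% and 70% attrition, close to the rescaled values. The gap therefore comes from the carried-forward zeros and not from lost information. On the unit scale the zeros also shrink the SE: it is 1.77 at full response and 1.01 at 70% attrition.

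**Units or d.** At 50% response the SD of the carried-forward change is 16.7, so the alternative on the d scale is 16.7 × 5/23 ≈ 3.6 units, not 5. The protocol does not say which scale enters the calculator.

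**The case against.** **The planned 3-unit Bayes factor already helps.** This stands in part. Three units is 5 units at 60% response, and at 30% attrition this version does slightly better than rescaling (8% against 9.5%). But it is secondary and fixed, and at 70% attrition it leaves P(BF<1) at 37% against 23%.

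**The alternative is given as d = 0.22, and on that scale the drift is milder.** This stands. The alternative then shrinks with the SD, and at an observed difference of zero the BF stays at 0.33 whatever the attrition, so the SE effect disappears. The drift remains, because the estimate shrinks with p while the SD shrinks only roughly with √p.

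**Five units may already be the effect across everyone randomised.** The protocol does not say either way. That it excludes non-responders is an inference from the absence of a dropout allowance.

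**Non-responders may truly not have benefited.** The protocol itself expects those who respond well to be retained more often. If non-responders do not change, the smaller difference is the real average effect across users, and a BF nearer the null is right. This is why a reader who infers that the plan manufactures support for the null goes too far: that reading assumes equal benefit in non-responders and high attrition, and the documents establish neither.

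**Whether Bayes factors accompany the sensitivity analyses is analysis-plan detail.** On its own it would be. But this document itself fixes both the no-change rule and the size of the alternative, and it is their combination that causes the drift.

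**Conclusion.** The concern holds in a limited form. Following the stated rules, the Bayes factor moves towards the null as attrition rises whenever non-responders would have benefited similarly, and calling the no-change rule conservative does not carry over to a statistic used to favour the null.

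The size depends on attrition rates that are assumptions here. At 30% attrition the drift is small. From about 50% it is material. Even at 70% the BF at the expected estimate is still about 1 for a true 5-unit effect with the 5-unit alternative. The largest figures also require the alternative to be entered in units. The result further assumes similar attrition at both levels and a 5-unit target that does not already include non-responders. It is a cheap improvement worth making, and does not show that the plan's screening conclusions would be wrong.

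**What to change.** In the Analysis section:

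1. State the alternative in units per week (5, and 3 for sensitivity), and enter estimate and SE on that scale.
2. Report each Bayes factor also from the already planned imputed (or responder-only) estimate with its own SE. If imputation is used, module allocation should be in the imputation model; otherwise the imputed values dilute the effect again.
3. Where the carried-forward estimate is used, add a version with the half-normal SD multiplied by the observed response proportion.
4. Conclude for the null only if these agree.

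This takes a sentence or two and no new data. The cost is fewer firm no-effect verdicts when attrition is high: under a true null at 30% response, P(BF<1/3) falls from 73% to about 19% with rescaling. Part of the protection for working modules thus comes from a procedure that less often reaches 1/3 at all, which reflects how little 30% response can show.

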## Discussion

This study protocol describes the design of a factorial randomised controlled trial to determine the effectiveness of five intervention modules delivered within a smartphone app at reducing excessive alcohol consumption. To our knowledge, this will be the first study to examine the effectiveness of a smartphone app to reduce excessive alcohol consumption that has been developed based on empirical evidence and theoretical models.

This type of trial and analysis means we can independently assess each module to see which module is having the biggest effect. This also allows for on-going evaluation and optimisation of the app for future evaluation of an integrated treatment package. As each module was developed based on empirical evidence and theoretical models, the findings of this study will be able to inform behavioural science, theory and future public health interventions. The ‘pure control’ group in this trial was effectively those who received ‘low’ versions of every intervention module which lacked the BCTs or intervention component being assessed in the ‘high’ version. Most popular alcohol reduction apps include almost no BCTs or mentions of theory [46], therefore the users receiving the ‘pure control’ were effectively receiving ‘usual care’ in this context.

The selection process of high priority modules for evaluation was intended to be systematic and transparent. However, it is possible that other researchers could have conducted a similar process and reached a different view. For example, it may have been of interest to evaluate the individual effect of goal-setting. Goal-setting was provided to all participants for two reasons. First, from a methodological perspective, we believed there was a pragmatic need to provide engaging content to all users, particularly those receiving low versions of all the modules, and around which access to other modules could be plausibly structured. Second, we thought the evidence-base on goal-setting was sufficiently robust that it would warrant inclusion in a future evaluation of an integrated app without support from a factorial screening experiment [121–123].

Our power calculation relied on a large estimated effect size (comparable with that of a face-to-face brief intervention) and may be considered somewhat unrealistic for a module within a digital intervention. The reason is that selecting smaller effect sizes would require larger numbers of participants and more time to recruit them. The Multiphase Optimization Strategy, which guides our research, emphasises agile screening experiments before running a definitive head-to-head trial of an optimised intervention against a control [106, 124]. We deal with the limitation of a somewhat unrealistic effect size for our power calculation by planning to supplement our inferential statistics by calculating Bayes factors. Bayes factors will provide useful information on the relative likelihood of smaller (more realistic) effects compared with the null given the data we obtain.

One strength of this intervention is that it is delivered by smartphone, so there will be no issues of availability or accessibility for the participants. The app can be used fully without an internet connection. The data is stored on the phone until an internet connection is available, when the data is then sent to the server. A limitation of this type of study is high attrition. We will send regular reminders for the one-month follow-up questionnaire and remind them of the incentives offered to reduce the risk of attrition. A practical issue may be recruiting enough participants to meet the numbers sufficient to meet the power for our analysis. We have planned for this issue by using best practices for app store optimisation and by promoting the app through trusted organisations such as Public Health England and University College London.

This study will evaluate the extent to which an app containing five intervention modules (self-monitoring combined with feedback, action planning, normative feedback, cognitive bias re-training, and identity change), developed based on theory and empirical evidence, can help reduce excessive alcohol consumption. Each intervention module will be independently assessed and the findings will be used to inform the content of a future app with an integrated treatment package that will be evaluated against a minimal control in a definitive randomised control trial with long-term outcomes. As the app and its intervention modules have been developed based on theoretical models and empirical evidence, these findings will also be able to inform future behaviour change interventions, theories and behavioural science.

## Abbreviations

BCT, behaviour change technique; DBCI, digital behaviour change intervention; RCT, randomised controlled trial.
